### Treatment delivery

3D conformal treatment must be delivered with at least six non-opposing conformal megavoltage photon beams. It is anticipated that a typical range of beam numbers would be 8 to 12, comprising of at least 6 co-planar beams and 1–2 non-coplanar beams. For treatment with conformal or VMAT arc techniques a typical beam arrangement would include two 180–220 degree arcs avoiding entrance through the contralateral side. A representative treatment plan is demonstrated in Fig. 1.

**Fig. 1 Fig1:**
[figure not shown]
Axial 3D conformal treatment plan of SABR for right kidney (A) and 3D reconstruction (B) showing multiple beam angles resulting in high-doses wrapping tightly around the target

### Treatment verification

All patients must undergo daily online image verification. Verification imaging must be capable of visualising the target with soft tissue matching as well as bone alignment. This would necessitate imaging with a Cone Beam CT (CBCT) or superior pre-treatment imaging modality.

### On-trial quality assurance (QA) program

This trial includes a comprehensive on-trial QA program. A pre-treatment radiotherapy QA technical review will be undertaken by the trial management team to provide independent validation of target definition, OAR contouring and plan quality. Post-treatment radiotherapy QA technical review will also be undertaken for all participating cases.

To ensure high plan quality and adherence to OAR dose limits, treatment plans will be assessed using knowledge based planning (KBP) prior to treatment. A RapidPlan model in the Eclipse treatment planning software (Varian Medical Systems, Palo Alto, USA) will be created based on the first 55 kidney SABR patients treated at Peter MacCallum Cancer Centre. The model will be applied to the first 20 patients recruited to the current trial to determine applicability to various planning systems and techniques used in this multi-centre trial. The model will then be used to determine if sufficient sparing of OARs has been achieved for each patient enrolled in the trial, based on previously achieved plan quality. This information will be communicated to the individual centres with the option to change the treatment plan prior to treatment if deemed appropriate given potential plan quality improvements and time and resource limitations.

### Adverse event reporting

All adverse events (AE) are to be reported between baseline and completion of study follow-up. All non-serious adverse events (including anticipated and unanticipated device related adverse events) shall be recorded in the trial database via adverse event CRFs. Internal statistical analysis of this data shall be performed at the times specified in the protocol and investigators and responsible HRECs will be advised of any safety issues which emerge during this process. Serious adverse event (SAEs) are to be reported to the Trial Coordinating Centre by the trial site within 24 h of being identified, from the commencement of radiotherapy to 90 days after the last fraction of radiotherapy. The investigator is responsible for notifying the responsible HRECs and Research Governance Officers as per local ethical and regulatory guidelines.

### Imaging sub-study 1: Evaluation of renal function change in response to SABR

Preservation of renal function is a major objective of kidney SABR. We will obtain split function nuclear medicine studies at baseline and 12, 24, 42 and 60 months after SABR for each patient enrolled in this trial. We will use deformable image registration to register the CT component of each DMSA SPECT/CT with the treatment planning CT, and apply this registration to the SPECT data. This will result in a 3D map of the DSMA uptake in the same spatial frame of reference as the planned radiotherapy dose. Based on this, we will then determine the change in DSMA uptake with radiation dose, and link any change as observed on imaging with clinical toxicity. Understanding the renal toxicity dose response will inform dose constraints on future patients. This information can further be used to optimise treatment plan quality in future renal SABR patients to minimise the dose to the functional components of the kidney.

### Imaging sub-study 2: Evaluation of renal function change in response to SABR

Multiparametric MRI (mpMRI) including diffusion weighted imaging (DWI) and dynamic contrast enhanced (DCE) MRI will be acquired in a subset of patients before treatment (baseline) and at 3 months and 12 months after SABR. DWI will be obtained using an echo-planar imaging sequence in the coronal plane with b-values of 50, 400 and 800 mm^2^/s, with the use of respiratory gating to reduce the effect of motion. DCE MRI will be obtained using a 3D T1-weighted TWIST sequence, in the coronal plane at an oblique angle so the entire affected kidney and the aorta are within the field of view. DCE MRI will be acquired during free breathing and 3D motion correction algorithms will be applied afterwards to reduce the effect of motion. Apparent diffusion coefficient (ADC) maps will be computed from the DWI data, and semi-quantitative and pharmacokinetic maps computed from DCE MRI data. Tumour contours will be drawn on the ADC maps and DCE MRI data, and relevant parameter statistics extracted. The change in each MRI parameter will be computed relative to baseline MRI, and correlated with the changes in tumour volume shown on follow-up CT relative to baseline CT, to assess whether DWI or DCE MRI parameters indicate treatment response earlier than conventional morphological CT based measures given by RECIST criteria [24] as shown in our exploratory study [25].

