### Sample size and study duration

In total, 70 patients are required for this study. It is anticipated that it will take 36 months to complete target accrual. The sample size of 70 patients was chosen to provide sufficiently narrow confidence intervals for clinical outcomes. If up to 15% of participants do not proceed to treatment, or die or are lost to follow-up before experiencing a local progression in the first year, and assuming the freedom from local progression (FFLP) at 1-year is 90%, the corresponding two-sided 95% confidence interval will be 79–96%. A 1-year freedom from local progression of 80% or less will be considered undesirable and not worthy of proceeding to a future randomised study against other treatment modalities. The freedom from local progression at 1-year is expected to be around 90%. With those assumptions, the proposed sample size will have 80% power with 10% alpha to test the null hypothesis that the FFLP at 1-year is 80% or less. The study end date is deemed to be the date of last data capture, which will be when the final participant completes the 5 year follow-up visit. Participant assessments are tabulated in Table 2.

**Table 2 Tab2:** Participant Assessments

ASSESSMENTS	Pre-Registration^a,b^	Post Treatment^c^													Post Progression^f^
		4 wks	3 mths	6 mths	9 mths	12 mths	18 mths	24 mths	33 mths	42 mths	51 mths	60 mths	Annually thereafter^d^	Progression^e^	Annually
Informed Consent	✓														
Informed consent for Health Economics data^g^	✓														
CT (Thorax/Abdomen)	✓^h,i^			✓	✓	✓	✓	✓	✓	✓	✓	✓	✓	✓^h,i^	
Split Renal Function Test (DMSA SPECT/CT) and calculated GFR (Cr-51 EDTA) ^j^	✓					✓		✓		✓		✓	✓^j^		
Whole body bone scan	✓													✓	
Clinical Consultation	✓		✓	✓	✓	✓	✓	✓	✓	✓	✓	✓	✓	✓	
Eligibility confirmation	✓														
Blood Tests^k^ and eGFR ^l^	✓	✓	✓	✓	✓	✓	✓	✓	✓	✓	✓	✓	✓	✓	
QLQ-C30 questionnaire ^m^	✓	✓	✓	✓	✓	✓	✓	✓	✓	✓	✓	✓			✓^m^
Adverse Event Reporting	✓	✓	✓	✓	✓	✓	✓	✓	✓	✓	✓	✓	✓	✓	
Survival Status															✓
MRI Sub study^n^															
Informed Consent	✓														
Multiparametric MRI	✓		✓			✓									

^a^To be done within 8 weeks of registration

^b^Treatment to commence within 6 weeks of registration

^c^Calculated from the date of the last radiotherapy fraction given. Post treatment follow-up to continue until both local and distant progression has been recorded

^d^After participant has both local and distant progression documented, annual survival status will be collected

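### The MRI sub-study aims to show response earlier than CT size, but without a 3-month size comparator its planned correlation mainly supports early prediction of later CT change

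*Protocol article*

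**What the plan says.** Four statements in the Protocol article bear on this point.

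- **MRI visits.** Imaging sub-study 2 says that multiparametric MRI "will be acquired in a subset of patients before treatment (baseline) and at 3 months and 12 months after SABR". The MRI row of Table 2 (Sample size and study duration) agrees.
- **CT visits.** The CT row of Table 2 is ticked at pre-registration, then at 6, 9 and 12 months and at every later visit, and at progression. The 4-week and 3-month cells are blank.
- **Analysis.** The change in each MRI parameter from baseline is to be "correlated with the changes in tumour volume shown on follow-up CT relative to baseline CT".
- **Purpose.** The analysis is meant "to assess whether DWI or DCE MRI parameters indicate treatment response earlier than conventional morphological CT based measures", with RECIST named as the source of those CT measures.

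On what is taken from the MRI, the same section says: "Tumour contours will be drawn on the ADC maps and DCE MRI data, and relevant parameter statistics extracted". It does not list tumour size among those statistics and does not name MRI size as a comparator. Study objectives and hypothesis classes the MRI work as exploratory and confined to a subset of patients.

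**The concern.** To say that one marker shows response earlier than another, one needs to know the state of the second marker when the first one changed. At 3 months, the only early MRI visit, the plan names nothing that records tumour size. Suppose the 3-month ADC or DCE change correlates strongly with CT shrinkage at 6, 9 or 12 months. Two explanations fit equally well. Either the functional parameter changed before size did, or size had already begun to change at 3 months and would have predicted the later CT just as well. The stated analysis does not separate them.

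At stake is the sub-study's conclusion. A report that MRI is earlier than RECIST could encourage the use of functional MRI where a plain size measurement at the same visit might have served.

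**Working it through.** No sample size, power or other figure is given for the sub-study, so there is none to reproduce. The check is of the schedule against the inference.

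**Step 1. Visits in the first year (Table 2)**

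| Visit | MRI | CT |
|---|---|---|
| Pre-registration | yes | yes |
| 4 weeks | no | no |
| 3 months | yes | no |
| 6 months | no | yes |
| 9 months | no | yes |
| 12 months | yes | yes |

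One of the two post-treatment MRIs (12 months) has a CT at the same visit. The first routine CT follows the first post-treatment MRI by 6 − 3 = 3 months.

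**Step 2. What each pattern can show about order**

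- *MRI changed at 3 months, no CT response at 6 months.* Barring shrinkage followed by regrowth, size had not responded at 3 months either. MRI was earlier, and the plan can show it.
- *MRI changed at 3 months, CT response at 6 months.* Size may have responded before or after 3 months. The order is unknown.
- *MRI unchanged at 3 months, CT response at 6 or 9 months.* CT is seen first, but no MRI was done at those visits. The MRI change may have come at the same time or sooner. The order is unknown.

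So the data inform the order in some patients and not in others. The document does not say how common each pattern is. The stated correlation also does not make this separation.

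**Step 3. Illustration of how the visits affect apparent order**

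Assume that MRI and CT size respond at exactly the same true time T, exponential with median m months. Both the distribution and the medians are assumptions. This ranks first detection, which is not the planned analysis, so the results are not estimates of bias in it.

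- MRI seen first: P(T ≤ 3) = 1 − 2^(−3/m)
- CT seen first: P(3 < T ≤ 9) = 2^(−3/m) − 2^(−9/m)
- Same visit, or neither by 12 months: 2^(−9/m)

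| Assumed m | MRI first | CT first | Tie or neither |
|---|---|---|---|
| 2 | 65% | 31% | 4% |
| 3 | 50% | 37.5% | 12.5% |
| 6 | 29% | 35% | 35% |
| 9 | 21% | 29% | 50% |

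With a size measure added at 3 months, the MRI-first column falls to 0% in every row, as it should when the true times are equal. The CT-first column does not change, because MRI is still absent at 6 and 9 months. The visit grid can thus create an apparent order in either direction.

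**The case against.** The strongest reply is that the aim can be read as early prediction: does the 3-month MRI foretell what later CT will show? The planned correlation answers that, and the objective as worded under Study objectives and hypothesis is broader still, asking about the usefulness of MRI as a response biomarker. This stands as far as it goes, but Imaging sub-study 2 itself words the aim as a comparison of timing with CT.

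A second reply is that an article need not list every MRI statistic, and that contours on the 3-month images can yield a size. This also stands. The point therefore does not rest on an omitted detail. It rests on the stated schedule, analysis and aim, which do not fit together.

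A third reply is that MRI size is not CT/RECIST size, so adding it changes the comparator. That is a fair limit on the fix below.

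A reader might infer more than the document supports:

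- *That the schedule guarantees MRI will look earlier.* It does not. CT alone is done at 6 and 9 months, so the grid can also favour CT.
- *That no tumour size is available at 3 months.* None is scheduled by CT, but one could be derived from the MRI contours.
- *That no data from the sub-study could show MRI to be earlier.* A 3-month MRI change followed by a 6-month CT without response would show it in that patient.

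**Conclusion.** The mismatch between aim and analysis is real but partial. The planned correlation can support a claim that 3-month MRI change predicts later shrinkage on CT. It supports a claim of an earlier signal than CT only in part, because no 3-month size comparator is named and size at that visit might predict equally well. This rests on the Table 2 schedule and the analysis stated in the article. It does not depend on the assumed response times in the illustration.

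The consequence is small. The work is exploratory, done in a subset at participating sites, and does not touch the primary endpoint or the test of 1-year freedom from local progression. This is a worthwhile improvement, not a flaw in the trial.

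**What to change.** Derive tumour diameter and volume from the baseline and 3-month MRI, which are already to be acquired and contoured. Relate 3-month ADC/DCE change and 3-month MRI size change, each in turn, to CT size change from baseline to 12 months. Then report what ADC/DCE adds once 3-month MRI size change is accounted for. State which CT measure is the target, since the section correlates with volume but names RECIST measures as the comparator.

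If this is not wanted, restate the aim as early prediction of later CT change and drop the comparison of timing.

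The cost of the first route is a little extra measurement per scan and one added exploratory analysis, with no extra scan or visit. Its limitation is that MRI size stands in for CT/RECIST size at 3 months, which the report should say. The second route costs only a change of wording.

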### Health economics evaluation

An economic evaluation will be conducted to estimate the incremental cost-effectiveness of SABR compared with current therapies (RFA/cryotherapy/surgery) for the treatment of patients with RCC. In the first instance, this will assess the within study costs and outcomes associated over the 5 years of the study. Subsequently, a Markov model will be developed using data on SABR from FASTRACK II and historical data on the comparators to assess the incremental cost-effectiveness of SABR compared with current therapies for the treatment of inoperable RCC.

The outcomes of the economic evaluation will be presented as cost per additional quality adjusted life year (QALY) gained. For SABR, QALYs will be estimated by applying utility values derived from the QLQ-C30 [26] by the time spent in each health state (e.g. progression free, progressed) and summed to calculate the total number of QALYs associated with SABR throughout the defined time-horizon. Utility values for the comparator technologies will be sought from the literature. In the absence of published values for those technologies, it will be assumed that there is no difference in utility values between therapies for a given health state.

Costs will be estimated taking into account the direct health care resources used for the delivery of SABR, associated hospital visits and the use of other medical services. Australian patients will be consented for access to administrative claims data from Medicare in order to capture outpatient medical and pharmaceutical services. Indirect patient costs (e.g. travel time and clinic time away from usual activities) will be assessed via a patient completed questionnaire, to be administered at the time of completing HRQoL questionnaires. Costs for the comparators will be based on existing scheduled fees and hospital costs known to apply to current therapies, supplemented with information on outpatient service use as informed by the data from this study.

Resource use will be valued using hospital-specific costs and scheduled fees for medical services and procedures. Mean estimates of costs will be used and Bayesian credibility intervals (BCI) will be generated by boot-strapping the data. The robustness and validity of the cost-effectiveness analysis will be explored using both a deterministic one-way sensitivity analysis and a probabilistic sensitivity analysis.

### Statistical considerations

Baseline characteristics will be summarised using descriptive statistics including counts and percentages for categorical variables and mean, standard deviation (SD), median and range for continuous variables. The Kaplan-Meier method will be used to estimate the OS, FFLP and freedom from distant progression. Annual estimates will be provided alongside 95% CI. An exploratory analysis will be carried out assessing the impact of baseline and treatment characteristic on OS using a Cox proportional hazard model. Cumulative incidence curves for cancer related death will be provided assuming competing risks with non-cancer related death as a competing event. Cumulative incidence curve for Grade 3+ toxicity will be provided assuming competing risks with death not related to treatment considered as a competing risk. A table with the frequency of worst AE grade experienced will also be provided for each individual AE type.

Change over time in renal function (serum creatinine, eGFR using CKI-EPI equation, split renal function and calculated GFR using nuclear medicine assessments) will be described using linear mixed models. The linear mixed model will include time as fixed effect (as a factor) and patients as a random effect. Mean and 95% confidence intervals will be calculated for each time point and the data will be displayed graphically using contrast from the linear mixed models. Changes from baseline will also be estimated using contrast from the linear mixed model. The impact of medical factors on renal function decline will be assessed by including relevant variables as independent variables in the linear mixed model.

No imputation of missing values and no adjustments for multiplicity are intended. This trial aims to a) describe clinical outcomes of patients with RCC treated with SABR and b) assess whether it is worthwhile conducting a future large randomised trial against other treatment modalities. The descriptive part of the study will use 5% alpha to provide two-sided 95% confidence intervals for clinical outcomes while the hypothesis testing on the FFLP at 1 year will use a one sided test with 10% alpha.

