### Study design

The Trans-Tasman Radiation Oncology Group (TROG) 15.03 FASTRACK II clinical trial is a single arm, multi-institutional phase II study conducted in collaboration with the Australian and New Zealand Urogenital and Prostate Cancer Trials Group (ANZUP). The trial will recruit 70 participants over a 3-year period, with patient follow-up to 5 years from the end of accrual. All participants will receive SABR as definitive treatment for their primary RCC.

The study population is patients with biopsy confirmed primary RCC with a single lesion within a kidney. The intervention is a single fraction SABR with one of two fractionation schedules selected based on tumour size: a single fraction of 26Gy is used for tumours ≤4 cm in maximum diameter, with 42Gy in three fractions delivered for tumours > 4 cm in maximum diameter. While biological equivalent dose estimation based on linear quadratic formula can be unreliable to estimate the effect of doses >10Gy per fraction, this model is still the most commonly used to describe iso-effectiveness of alternate SABR fractionation regimens. The radiosensitivity of the two most common human RCC cell lines (Caki-1 and A498) has been observed in the laboratory to vary with α/β values estimated to be 2.6Gy or 6.9Gy, depending on the cell line [23]. The biological effective dose for tumour effects when using the dose/fractionation cohorts proposed with an α/β of 6.9Gy are 123Gy for 26Gy in 1 fraction, and 127Gy for 42Gy in 3 fractions. When altering the model to use the alternate α/β of 2.6Gy, the biological equivalent dose is 286Gy for 26Gy in 1 fraction and 268Gy for 42Gy in 3 fractions. These dose calculations show that the cohorts are relatively iso-effective across a reasonable range for potential tumour effects in the study.

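### If patients' renal trajectories diverge over 5 years, the renal-function mixed model as written gives late changes from baseline confidence intervals that are too narrow

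*Protocol article*

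**What the plan says.** The section Statistical considerations of the protocol article plans linear mixed models for serum creatinine, eGFR, split renal function and nuclear medicine GFR. It specifies them as follows: "The linear mixed model will include time as fixed effect (as a factor) and patients as a random effect". Visit means with 95% intervals are taken from the model, and "Changes from baseline will also be estimated using contrast from the linear mixed model". It also states that "The descriptive part of the study will use 5% alpha to provide two-sided 95% confidence intervals for clinical outcomes".

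The same section expects decline to vary with patient characteristics: "The impact of medical factors on renal function decline will be assessed by including relevant variables as independent variables".

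The visits span a long period. Table 2 has blood tests and eGFR before registration, at 4 weeks, and at 3, 6, 9, 12, 18, 24, 33, 42, 51 and 60 months: 12 time points up to year 5. For the nuclear medicine tests, Imaging sub-study 1 says "We will obtain split function nuclear medicine studies at baseline and 12, 24, 42 and 60 months after SABR".

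The article names no random slope, residual covariance structure or robust standard error for these models.

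**The concern.** With time as a factor, a single patient random effect is most naturally read as a random intercept with independent residuals. That structure makes baseline and 60 months as strongly correlated as baseline and 4 weeks. With complete data, every change from baseline then has the same standard error.

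This is adequate if patients' curves run parallel. If they spread apart, the variance of a change from baseline grows with time. The model averages over that growth and reports too small a standard error for the late visits.

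Renal function is a key secondary endpoint, and Imaging sub-study 1 calls its preservation a major objective. The trial's first stated aim is descriptive, so the intervals are themselves a result. At stake is a 5-year renal change that looks better known than it is.

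**Working it through.** **The plan's own figure.** The article gives no figure for the renal model. Its only relevant number is the allowance for 15% attrition in year 1: 70 × 0.85 = 59.5, taken here as n = 60. The stated 79–96% interval for the primary endpoint is consistent with this size: the exact binomial interval for 53/59 is 79.2–96.2%.

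**Inputs.** Visit times come from Table 2 and Imaging sub-study 1, in years and up to 60 months, with 4 weeks taken as 1 month. Assumed, because the documents give no variances: residual SD σe of 6 or 8 mL/min, linear slope SD σb of 0 to 3 mL/min/year, and complete data. The between-patient SD of level cancels from every formula below.

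**Formulas.**
- Within-patient variance seen by the random-intercept model: s² = σe² + σb² × V, where V is the variance of the J visit times (divisor J − 1).
- Model SE of any change from baseline: √(2s²/n).
- True SE of the change at time t: √((σb²t² + 2σe²)/n).
- Coverage: 2Φ(1.96 × model SE / true SE) − 1.

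**Spread of visit times.**
- eGFR: J = 12, Σt = 21.583, Σt² = 71.007, so V = (71.007 − 21.583²/12)/11 = 2.926.
- Nuclear medicine: J = 5, Σt = 11.5, Σt² = 42.25, so V = (42.25 − 11.5²/5)/4 = 3.95.

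**Worked case (eGFR, σb = 2, σe = 6).**
- s² = 36 + 4 × 2.926 = 47.70, and model SE = √(95.41/60) = 1.26 at every visit.
- At 60 months the true SE is √((100 + 72)/60) = 1.69. The ratio is 0.745 and coverage 85.6%. The 95% half-width is 1.96 × 1.26 = 2.5 mL/min where 1.96 × 1.69 = 3.3 is needed.
- At 4 weeks the true SE is 1.10. The ratio is 1.15 and coverage 97.6%.

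**Coverage of a nominal 95% interval (%).**

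| Slope SD | Residual SD | eGFR, 4 weeks | eGFR, 60 months | Nuclear, 12 months | Nuclear, 60 months |
|---|---|---|---|---|---|
| 0 | any | 95.0 | 95.0 | 95.0 | 95.0 |
| 1 | 8 | 95.5 | 93.3 | 95.6 | 93.5 |
| 1 | 6 | 95.8 | 92.1 | 96.0 | 92.5 |
| 2 | 8 | 96.7 | 89.0 | 96.9 | 89.9 |
| 2 | 6 | 97.6 | 85.6 | 97.8 | 87.2 |
| 3 | 8 | 98.0 | 83.9 | 98.2 | 85.9 |
| 3 | 6 | 99.0 | 79.6 | 99.1 | 82.6 |

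Coverage depends only on the ratio of slope SD to residual SD. The rows therefore also serve measures in other units, such as creatinine or split function, at the same ratio. Intervals change from too wide to too narrow at about 24–33 months for eGFR and 24–42 months for the nuclear tests.

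**Simulation check.** In 1,000 simulated trials fitted by REML (eGFR schedule, slope SD 2, residual SD 6), coverage was 97.8% at 1 month and 85.8% at 60 months with complete data. With about 10% dropout per year it was 96.6% and 83.9%. With slope SD 0 it stayed at about 95%.

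**A different trajectory shape.** Suppose each patient's loss builds up linearly over 12 months and then stays constant, with SD of loss 4, 6 or 10 mL/min and residual SD 6. Replace t by min(t, 1) in the formulas. On the nuclear schedule V becomes 0.2. For SD 6, s² = 36 + 36 × 0.2 = 43.2, model SE = √(86.4/60) = 1.20 and true SE = √((36 + 72)/60) = 1.34, so coverage is 92.0%. Across the three SDs, nuclear coverage is 93.6%, 92.0% and 88.6%, the same at every post-treatment visit. For eGFR at 60 months it is 93.3%, 91.5% and 87.2%. Late intervals are still too narrow, but no nuclear medicine interval is too wide.

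**The case against.** The strongest objection is that the article does not literally specify a random intercept and nothing else. It condenses a full protocol, and neither that nor a statistical analysis plan is at hand. Residual covariance, degrees of freedom and fallbacks are often settled there. This stands as a limit on the reading: a reader might infer that a richer structure has been ruled out, and the text does not say so. It does not remove the point, because the article writes the model out and takes the intervals from it, and the wording as it stands leads an analyst to equal correlation.

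Second, a reader might infer that the late intervals are certain to be wrong. The documents give no slope variance, residual variance or trajectory shape. Planning to examine factors for decline suggests that patients differ, but not by how much. With parallel trajectories there is no error, and with slope SD 1 the loss is only 2 to 3 points. This stands, so the point is conditional.

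Third, the tempting symmetrical statement, late too narrow and early too wide, depends on steady divergence. If losses plateau by 12 months, the early half fails on the nuclear medicine schedule. This stands too.

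Fourth, the analysis is secondary and descriptive. The only hypothesis test is on 1-year freedom from local progression, and no decision rule uses the renal intervals. With complete data the mean changes themselves are unaffected. All of this is correct and limits the weight of the point.

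**Conclusion.** The point holds in conditional form. As written, the model implies equal correlation between any two visits over 5 years. If renal trajectories diverge, intervals for late changes from baseline will be too narrow, and this survives a change from linear to plateau trajectories. That early intervals are too wide follows only if divergence is steady.

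The size rests on assumed variances. With residual SD 6–8 mL/min, coverage of the 60-month eGFR change runs from 95% with no slope variation, through 92–93% at slope SD 1 and 86–89% at SD 2, to 80–84% at SD 3. The nuclear medicine schedule gives slightly better figures.

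The documents do not support the stronger conclusions that the renal results will be wrong or that the trial's main finding is at risk. The primary endpoint and the sample size are untouched. The correction is still worth making, because it stays valid if trajectories turn out to be parallel, whereas the stated model fails if they do not.

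**What to change.** Keep time as a factor and state the covariance or standard-error method in the protocol or analysis plan, before the renal data are analysed. Either of these would do:

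- Report standard errors clustered by patient, with a small-sample correction. This does not depend on trajectory shape, which matters because a linear random slope would not match a plateau.
- For eGFR and creatinine, add a patient random slope in time or a time-decaying residual covariance.

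An unstructured covariance is practical only for the five-visit nuclear medicine measures, with 5 × 6/2 = 15 parameters. Over the 12 eGFR time points it needs 12 × 13/2 = 78 parameters from at most 70 patients, so it is not a sensible default there.

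The cost is a short change of wording, somewhat wider late intervals and some convergence checks. No new data, visits or patients are needed.
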